### Strategies for obtaining the adequate recruitment of the participants

2.14

The participants will be recruited from the clinics of *Universidade Nove de Julho*. A researcher ([name]) will perform the exam to detect halitosis in a reserved room at the university. Treatment will be performed immediately after the diagnosis. The participants will be counseled with regard to oral health and will receive a set of instructions for performing daily oral hygiene. If they wish to withdraw their consent, there will be no loss for them. It is expected that patients will complete their participants, due to the benefit of halitosis reduction. Data from those who discontinue will not be used for analysis. After 1 week, all patients will be asked to return to *Universidade Nove de Julho* for the reevaluation of halitosis.

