**Methods::**

A randomized, controlled trial is proposed. The patients will be divided into 2 groups: G1: older adults who wear complete dentures and will be treated with tongue scraper (n = 20); G2 older adults who wear complete dentures and will be treated with PDT (n = 20). If the halitosis persists, the participants will be submitted to hygiene procedures for the mucosa and dentures. The evaluation of halitosis will be made before and after treatments, with OralChroma^TM^. If the halitosis is solved, the participants will return after 1 week for an additional evaluation. Oral Health Impact Profile (OHIP-14) will be administered by a calibrated examiner on the day the patient history is taken (baseline) and 1 week after treatment for halitosis.

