### Characterization of the study

2.7

The experimental design will consist of 2 groups: G1-older adults with halitosis (SH2 ≥ 112 ppb) who wear complete dentures and treatment with a tongue scraper (n = 20); G2-older adults with halitosis (SH2 ≥ 112 ppb) who wear complete dentures and treatment with PDT (n = 20). The evaluation of halitosis will be performed at baseline (1st session), after treatment with a tongue scraper or PDT (1st session) and after 1 week (2nd session) (Fig. 3).

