### Assessment of halitosis

2.9

This is the primary outcome of the study. The portable Oral Chroma^TM^ (Abilit, Japan) will be used for the assessment of halitosis, which is a highly sensitive semiconductor gas sensor. The participant was instructed to rinse with cysteine (10 mM) for 1 minute, with the aim of selecting the gases produced by bacteria degradation. A syringe will be placed in the patient's mouth with the plunger completely inserted and the participant will breathe through the nose with the mouth closed for 1 minute, being careful not to touch the tip of the syringe with the tongue. The plunger will then be withdrawn to fill the chamber with air. This procedure will be repeated. The tip of the syringe will be cleaned to remove the saliva. The gas injection needle will be placed on the syringe and the plunger will be adjusted to 0.5 ml. This air will be injected into the input of the device in a single motion. When connected to a computer, the specific software accompanying Oral Chroma^TM^ produces a graph with peaks and values corresponding to the concentrations of VSCs (from 0 to 1000 ppb) with considerable precision after a period of 8 minutes. The results are stored in both the program and the device. As it is a device, Oral Chroma^TM^ is a blind assessor.

To standardize the readings, the exam will be performed in the morning and the participants will be instructed to avoid the ingestion of some strong spices, onion, garlic, and alcohol as well as the use of an antiseptic mouthwash 48 hours prior to the exam. The participants will also be instructed to abstain from coffee, mints, chewing gum, oral hygiene products, and personal hygiene products with perfume (after shave, deodorant, creams, or tonic) and brush only with water on the day of the test as well as not eat anything at least 2 hours prior to the test.^[23–25]^

*Analysis of Oral Health Impact Profile* (OHIP-14 questionnaire): The OHIP-14 is a shortened version of the original OHIP questionnaire used for the evaluation of the impact of oral health on quality of life. The items are distributed among subscales (functional limitation, pain, psychological discomfort, physical disability, psychological disability, social disability, and social handicap). The OHIP-14 will be administered by a calibrated examiner on the day the patient history is taken (baseline) and 1 week after treatment for halitosis.

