### Statistical analysis

2.13

The Lilliefors test will be used to determine the normality of the data. If normality is demonstrated, analysis of variance (*t* test student, Bioestat 5.3, Pará, Brazil) will be used to compare continuous and dependent variables among G1 and G.2. If non-normal distribution is demonstrated, Mann Whitney test will be used. The baseline data will be compared to the data collected at 1 week follow-up evaluation. A *P*-value < .05 will be considered indicative of statistical significance. The *χ*^2^ test will be used to compare categorical variables among G1 and G2, at baseline and the 1 week evaluation. These data will be expressed as mean ± standard deviation.

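### Section 2.14 excludes everyone who discontinues, which fixes a completers-only comparison and discards first-session readings of the primary outcome; separately, the abstract and main text disagree on who is assessed at 1 week

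*Protocol article*

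**What the plan says.** Section 2.14 gives the rule for patients who leave: "Data from those who discontinue will not be used for analysis". Just before it, the section notes that consent may be withdrawn without penalty and predicts completion because patients will benefit from reduced halitosis. The next sentence says: "After 1 week, all patients will be asked to return to" the university for re-evaluation.

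Section 2.7 schedules readings at baseline, "after treatment with a tongue scraper or PDT (1st session) and after 1 week (2nd session"), with no condition on response. Section 2.9 says of the halitosis assessment: "This is the primary outcome of the study". Section 2.13 names the comparison: "The baseline data will be compared to the data collected at 1 week follow-up evaluation".

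The Methods paragraph of the abstract differs on the 1-week visit. It says first "If the halitosis persists, the participants will be submitted to hygiene procedures for the mucosa and dentures", and later "If the halitosis is solved, the participants will return after 1 week for an additional evaluation".

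**The concern.** Randomisation protects the comparison only if patients are analysed whatever happens after allocation. A rule that removes those who discontinue lets a post-treatment event decide who is counted. If patients with little improvement are less likely to come back, and more of them are in one arm, that arm looks better than it is. Patients know whether they received a scraper or dye and laser, so loss that differs between arms is plausible.

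The rule is also wasteful. Each treatment is given once, and the immediate reading is taken in the same session. A patient who fails to return at 1 week has therefore usually contributed two readings of the primary outcome already, and the rule deletes both.

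The disagreement over the 1-week visit matters because Section 2.13 builds its named comparison on that visit.

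**Working it through.** **The plan's own figure.** Section 2.2 gives 18 per group. It cannot be reproduced: the effect-size formula is in a figure that is not shown, and no readable effect size, SD or power is given. This is not an error in the plan, and 18 is taken as stated.

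**Margin for loss (document figures only).**
- Randomised per arm: 20 (Section 2.6). Calculated: 18 (Section 2.2).
- 20 − 18 = 2 per arm, or 2/20 = 10%.
- Section 2.2 adds about 5% if normality is rejected: 18 × 1.05 = 18.9, rounded up to 19. Then 20 − 19 = 1 per arm, or 5%.

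**What the margin means for power (assumption: 18 was set for 80% power, two-sided 5%).** The implied standardised difference is d = √(2/18) × (1.960 + 0.842) = 0.93. Power with n per arm is Φ(d√(n/2) − 1.96).

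| n per arm | 20 | 18 | 16 | 14 |
|---|---|---|---|---|
| Power | 84% | 80% | 75% | 70% |

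**Bias from removing discontinuers (assumed: true resolution 10/20 in each arm, loss in one arm only).** The observed rate is resolved patients remaining divided by patients remaining.

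| Removed from one arm | Observed rate there | Other arm | False gap |
|---|---|---|---|
| 2 unresolved | 10/18 = 55.6% | 50% | +5.6 points |
| 4 unresolved | 10/16 = 62.5% | 50% | +12.5 points |
| 2 resolved | 8/18 = 44.4% | 50% | −5.6 points |
| 4 resolved | 6/16 = 37.5% | 50% | −12.5 points |

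The last two rows show that the direction is not fixed. If 2 unresolved patients were lost from both arms, there would be no false gap, but both rates would read 55.6% instead of 50%.

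**Same effect on a continuous outcome (simulation on assumed values).** Inputs: 20 per arm, no true difference, log-scale SD 0.8, correlation 0.6 between immediate and 1-week values, t test at 5%, 4,000 runs. The patients with the worst immediate values were removed from one arm.

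| Share removed from one arm | 0% | 10% | 20% | 30% |
|---|---|---|---|---|
| False-positive rate | about 5% | about 7% | about 10% | about 13% |
| Spurious log difference | 0 | 0.09 | 0.16 | 0.23 |

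**Who is assessed at 1 week (no arithmetic).**
- Abstract: the return is tied to halitosis being solved, after a sentence sending persistent cases to hygiene procedures.
- Section 2.7: 1-week evaluation without condition.
- Section 2.14: all patients asked to return.

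The two main-text sections agree with each other, and the abstract differs from both.

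**The case against.** **The exclusion may only concern withdrawn consent.** The sentence stands close to the one on withdrawal, and data use after withdrawal can be limited. That much stands, and the fix allows for it. But the sentence covers all who discontinue, not only those who withdraw permission to use their data.

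**There may be little or no loss.** Only one visit a week later remains after the first session. The section predicts that patients will complete; it does not say that non-responders will leave. If everyone returns, the comparison stays as randomised. This stands, and it is why no size can be put on the bias. It does not defend the rule, which has an effect only when patients are lost.

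**Keeping earlier readings does not rescue a simple two-sample test at 1 week.** This is correct. A patient without a 1-week reading adds nothing to the t or Mann-Whitney test in Section 2.13. The remedy therefore needs a model or imputation that uses the earlier readings.

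**A stronger reading of the abstract is tempting.** A reader might infer that the 1-week test compares PDT responders with scraper responders only. The documents do not support that. The abstract says *if*, not *only*. It places the hygiene step before the reference to solved halitosis, so patients who resolve after hygiene may return as well. The main text recalls everyone.

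**Conclusion.** The completers-only rule is explicit and should be replaced. It discards primary-outcome readings already in hand and opens the comparison to bias if loss is related to response, which the document's own expectation about completion makes plausible.

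The size of the bias is unknown. On the assumed 50% resolution, losing 2 to 4 patients from one arm can move that arm's rate by about 6 to 13 points in either direction. The simulated false-positive rates likewise rest on assumed values and on loss of the worst responders from one arm. The margin of 2 per arm (1 if the non-normality correction applies) follows from the document's figures alone.

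The difference over the 1-week visit is a contradiction to be reconciled. It does not by itself show that the trial compares patients selected on response.

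**What to change.** Replace the sentence in Section 2.14 with:

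> All randomised patients are analysed in their assigned group using all readings obtained, as far as consent allows. The immediate post-treatment comparison includes every patient with that reading. The continuous 1-week comparison uses a likelihood-based repeated-measures model (or multiple imputation) on the baseline, immediate and 1-week readings, with a sensitivity analysis counting patients missing at 1 week as not resolved.

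Under a missing-at-random assumption, the model lets the immediate reading inform the 1-week comparison, so it can account for loss that depends on the immediate response. Section 2.13 should be brought into line with it. Counting missing patients as not resolved is itself an assumption, which is why it belongs in the sensitivity analysis.

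Reconcile the abstract with Sections 2.7 and 2.14 so that all three state the same 1-week population.

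The cost is a few sentences of wording, slightly more analysis work and possibly less favourable response rates. No extra patients or visits are needed beyond those Sections 2.7 and 2.14 already plan.

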## Discussion

3

Through the proposed clinical trial, we will evaluate the effect of PDT on halitosis in older adults who wear complete dentures, comparing this therapy to the use of a tongue scraper. PDT is an alternative therapeutic intervention for halitosis that diminishes the quantity of intraoral microorganisms, offers low toxicity,^[5]^ does not induce bacterial resistance, does not have side effects and preserves the oral microbiota.^[22]^

Halitosis is a common condition among older adults in nursing homes due to their greater frailty, poorer hygiene, greater risk of multi-morbidities, impaired cognition, and impaired functioning.^[30]^ However, few studies have analyzed the prevalence of halitosis in the older population, which, according to the World Health Organization is composed of individuals 60 years of age or older. In Thailand, the incidence of halitosis is high in the older population,^[11]^ whereas halitosis was mainly identified in older women who wore complete dentures in Turkey.^[12]^ A significant number of older adults wear dentures and this number has increased mainly in developed countries, at least with regard to a complete upper denture.^[31]^ Dentures themselves favor bacterial colonization, especially when associated with poor hygiene,^[18,32]^ which is a consequence of the limited dexterity and reduction in visual acuity in the older population, making it difficult to maintain adequate oral hygiene, which is indispensable to esthetic quality and the maintenance of oral health.

The surfaces of complete dentures are subject to colonization by oral microbiota, which can undergo changes when an individual becomes edentulous, with an increase in the presence of acidophilic bacteria in the oral cavity.^[33,34]^ Few studies have addressed the oral microbiota in patients who use complete dentures. It is reported, however, that changes in this microbiota stem from factors such as age, systemic condition, changes in salivary flow, differentiated dietary habits, the use of medications, poor hygiene, and changes in salivary pH,^[31]^ which can increase the amount and proportion of microorganisms that favor the occurrence of halitosis.

Changes in general health have also been identified as etiological agents of halitosis of an extra-oral origin,^[5,6,13]^ such as lung diseases as well as gastrointestinal, hepatic, endocrine, and metabolic disorders.^[5,6,13]^ Some treatments for halitosis are well established, such as the use of a tongue scraper and mouthwash. However, tongue scrapers are not habitually used by Brazilians due to the discomfort caused to the papillae and the lack of a technique of standardized use.^[29]^ The tongue scraper used in the proposed study has soft bristles to avoid discomfort to the tongue and injury to the adjacent periodontium during use. Moreover, its anatomic design favors handling. The method employed will be the same as that described by Mota et al.^[24]^

The dosimetric parameters for PDT were chosen based on previous studies that report favorable results with the administration of this type of therapy.^[23–25]^ According to Mota et al,^[24]^ immediate positive results were achieved with PDT for the treatment of the dorsum of the tongue in adolescents, with a reduction in halitosis due to the reduction in the concentration of VSCs. However, as mentioned above, the effects of PDT on halitosis in older adults with complete denture have not yet been studied.
